## Materials and methods

2

This is a longitudinal observational study of a cohort, registered prospectively on ClinicalTrials.gov (NCT03446742). It going to be developed with a convenience sample of patients regularly attending a CRP based on exercise.

### Eligibility criteria

2.1

Subjects of both genders, with clinical diagnosis of CVD and/or cardiovascular risk factor, able to realize all the evaluations proposed and in accordance to the study procedures are going to be included. Patients with less than 30% of attendance during the period of the protocol are going to be excluded.

### Sample size

2.2

The sample size was based on rMSSD index^[36]^ because it presents the highest sample number necessary for this study, compared with the other main variables [6 minutes walking test^[37]^ and tumor necrosis factor (TNF)-alpha^[38]^]. A standard deviation of 17 ms, alpha risk of 5%, and beta of 80% was considered for the calculus, which resulted in 44 subjects.

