**Materials and methods:**

The study was prospectively registered at ClinicalTrials.gov (NCT03446742). Forty-four patient participants of a CRP will be evaluated. First, their risk stratification is going to be performed by 2 evaluators and their clinical, physical, and biochemical parameters are going to be measured. Then, the patients are going to be followed during 24 sessions during their CRP routines in order to identify appearance of their signals/symptoms. So, the patients are going to perform their cardiovascular rehabilitation routines for 6 months and then, their clinical, physical, and biochemical parameters are going to be measured again and they are going to be followed during 24 sessions during their CRP routines in order to identify the appearance of their signals/symptoms.

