#### Autonomic modulation

2.7.3

The autonomic modulation is going to be evaluated through the HRV analysis. For this analysis, the HR will be recorded beat-to-beat in a quiet room, with temperature controlled between 21° and 24° C and air relative humidity between 40% and 60%. The data collection is going to be done individually and the patients remain at rest in an orthostatic position for 30 minutes. The patients are going to be oriented to not consuming stimulant substances of the ANS such as alcoholic drinks, coffee, tea, soda, and chocolate for 24 hours before HRV analysis.

A heart rate monitor Polar RS800CX (Polar Electro OY, V800, Finland) is going to be used for HR record, and the data recorded are going to be transferred to the computer through the Polar Flow web service (https://flow.polar.com/).

For the data analysis, we are going to use 1000 consecutive RR intervals, after a digital filtering complemented by a manual filtering, to eliminate ectopic, premature, and artifacts beats, and only series with more than 95% of heart sinus beat are going to be included in the study.

Linear indices of HRV in the time and frequency domain are going to be used for HRV analysis. In the time domain, RMSSD (root mean square to the successive differences between each heartbeat) and SDNN (standard deviation of all normal RR intervals) are going to be calculated.^[46]^ In the frequency domain, the spectral components of low frequency (LF: 0.04–0.15 Hz) and high frequency (HF: 0.15–0.40 Hz) are going to be evaluated, in milliseconds squared (ms^2^) and normalized units (nu), and also the relation between LF and HF components (LF/HF). The spectral analyses are going to be calculated using the algorithm of Fast Fourier transform.^[46]^

In addition, the HRV is going to be also calculated through the quantitative analysis of Poincaré Plot, considering the following indices: SD1 (standard deviation of distances of diagonal points), SD2 (standard deviation of the distances from points to lines), and finally the SD1/SD2 that describes the ratio between short and long variations of RR intervals.^[46]^

All the HRV indices are going to be obtained using Kubios HRV Standard software – version 3.0.0 (Kubios, Biosignal Analysis and Medical Image Group, Department of Physics, University of Kuopio, Kuopio, Finland).

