### Data analysis

2.12

The normality of data is going to be analyzed using Shapiro--Wilk test. According to the distribution, the population characteristics will be presented, as mean and standard deviation for parametric distribution and median and interquartile interval for nonparametric distribution.

The relationship between the number of signals and symptoms of the patients and the scale degree of the protocols (1, 2, and 3) is going to be analyzed using Pearson correlation. The concordance degree of each protocol with the number of signals and symptoms are going to be determined using coefficient of intraclass correlation. To determine the efficacy of the risk stratification protocols as soon as clinical, physical, and biochemical parameters to previse signals and symptoms during the CRP, analysis of sensibility and specificity using ROC curve is going to be done. The sensibility, specificity, and predictive value (positive and negative) for the occurrence of events are going to be also registered. If the values of the area on the curve are ≥0.650, it will be considered significative.

To evaluate whether the clinical, physical, and biochemical modifications have influenced in the occurrence of signals and symptoms, the sphericity of the data will be verified by Mauchly test, and if the sphericity be violated, Greenhouse--Geiser correction will be performed. The comparison between the different moments of the clinical (cardiorespiratory parameters and autonomic modulation), physical (maximum isometric endurance, MIVC, cardiorespiratory fitness and physical activity level), and biochemical (IL-6, TNF-alpha, and IL-10) are going to be realized by repeated measures analysis of variance (ANOVA) and the possible differences between the moments will be performed by Bonferroni post-hoc.

The statistical significance difference adopted is going to be fixed in 5% with 95% of confidence interval. The analysis is going to be done on SPSS 15.0 version (SPSS Inc., Chicago, IL).

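### The 44 patients required for rMSSD are also the 44 taken in, so the stated power has no margin for the plan's own post-entry exclusions, and the attendance rule can discard complete first-phase data

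*Protocol article*

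**What the plan says.** Section 2.2 names the sizing variable, "The sample size was based on rMSSD index", and gives the inputs and the result: "A standard deviation of 17 ms, alpha risk of 5%, and beta of 80% was considered for the calculus, which resulted in 44 subjects". No loss allowance is among those inputs.

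The Abstract (Materials and methods) uses the same figure, "Forty-four patient participants of a CRP will be evaluated", and then lists what happens to these patients, starting with risk stratification and baseline measurement.

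Two rules act after entry. Section 2.1: "Patients with less than 30% of attendance during the period of the protocol are going to be excluded". Section 2.7.3, on the RR recordings from which rMSSD is computed: "only series with more than 95% of heart sinus beat are going to be included in the study".

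Section 2.4 sets two evaluations. Each is followed by 24 observed sessions, and 6 months of usual rehabilitation lie between the two blocks. Section 2.10 gives three sessions a week. Section 2.12 compares the moments by repeated measures ANOVA and assesses prediction of signals and symptoms by correlation and ROC analysis.

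**The concern.** A number derived from a power calculation is the number that has to be analysed. Here it is also the number that starts. Low attendance is known only after follow-up, and an inadequate RR series only after recording. Both rules can therefore only reduce the analysed number below 44, and the plan has fixed that number with nothing to spare. In a cohort with cardiovascular disease or risk factors, where section 2.11 lists pulse-rate changes among the most prevalent signals, some rejected series are foreseeable.

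At stake is the only power statement in the article, which holds as written only if every patient keeps a valid series at both evaluations.

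A second problem comes from the same attendance rule. Because it runs over the whole protocol, whether a patient stays in the first-phase prediction analyses depends on behaviour after the first outcome window has closed. That loses usable data and may select on later adherence.

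**Working it through.** **Inputs.** From section 2.2: SD 17 ms, alpha 5%, N = 44, and 80% read as power. Section 2.12 repeats the 5% level: "The statistical significance difference adopted is going to be fixed in 5% with 95% of confidence interval". A two-sided test is assumed because sidedness is not stated. Sections 2.4 and 2.12 give two moments, so the repeated measures ANOVA on rMSSD amounts to a paired comparison, and a patient with only one valid series adds nothing to it.

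**The plan's own figure.** 44 cannot be reproduced, because no detectable difference is given. Solving backwards for a paired comparison, with 17 ms taken as the SD of the change:

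difference = SD × (z₀.₉₇₅ + z₀.₈₀) / √n = 17 × (1.960 + 0.842) / √44 = 17 × 2.802 / 6.633 = 7.18 ms.

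The noncentral t distribution gives 7.35 ms.

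**Power with fewer pairs.** If 44 pairs give exactly 80%, the normal approximation for the same difference is

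power(n) = Φ(2.802 × √(n/44) − 1.960).

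This needs neither the SD nor the difference, so the missing effect size does not affect the relative loss. For n = 39: 2.802 × √(39/44) = 2.638; 2.638 − 1.960 = 0.678; Φ = 75.1%.

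| Pairs | Lost of 44 | Normal approximation | Noncentral t |
|---|---|---|---|
| 44 | 0 | 80.0% | 80.0% |
| 42 | 2 (4.5%) | 78.1% | 78.1% |
| 39 | 5 (11.4%) | 75.1% | 74.8% |
| 35 | 9 (20.5%) | 70.5% | 70.0% |
| 30 | 14 (31.8%) | 63.8% | 62.8% |

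The losses are assumptions, since the documents give none. As an illustration of how the rules combine, take 10% lost to attendance or withdrawal and 5% of series invalid at each moment, independently: 44 × 0.90 × 0.95² = 35.7, so about 36 pairs and 71% power. Reading 44 as a two-group figure instead (22 or 44 per group) gives 70–71% power at 20% loss, so the result does not depend on the paired reading.

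**Interval between evaluations.** 24 sessions / 3 per week = 8 weeks; with the 6 months that follow, about 8 months.

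**Attendance rule.** Six months is about 26 weeks, so 26 × 3 = 78 sessions. Scheduled sessions over the whole protocol: 24 + 78 + 24 = 126. The threshold is 0.30 × 126 = 37.8, so 38 sessions. A patient who attends all 24 first-phase sessions and then leaves reaches 24/126 = 19.0% and is excluded. Section 2.4 performs the risk stratification only in the first phase, and the 24 sessions that follow supply its outcome, so that patient has everything the first-phase prediction analysis needs.

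**The case against.** A reader might infer that the stated power is not delivered, or that the plan cannot keep all 44. The documents do not support either. They give no loss rate. Losing one or two patients costs at most 2 points. The attendance bar is low, and section 2 recruits patients who already attend regularly. Without an effect size it also cannot be proved that 44 contains no margin. All of this stands, and it makes the shortfall conditional.

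The 44 might mean evaluable patients, since both rules are worded as inclusion or exclusion from the study. The text does not say so, gives no replacement rule, and in the Abstract reads more naturally as intake. Figure 1, which reports the volunteers in each phase, is not shown and might bear on this and on who enters the first-phase analyses.

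A condensed article may leave expected attrition to a fuller document. That is fair, and the absence of an attrition estimate is not the point. The article itself fixes the required number, the intake and the exclusion rules, and as fixed they leave no room for one another.

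The 126-session denominator is a reading: it takes the rule to cover all three phases and counts scheduled sessions. It is the plain reading of the sentence, but an interpretation. Finally, a less demanding remedy, applying the 30% rule only to the two 24-session windows, would leave no attendance requirement in the six months whose effect the change analysis is meant to capture. That objection is right, and the fix has to respect it.

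**Conclusion.** The point holds in conditional form. Required number and intake are both 44, none of the stated inputs is a loss allowance, and the plan's own rules can only lower the number analysed on rMSSD. If 44 is the bare requirement for 80% power (two-sided 5%), power is about 78% with 42 pairs, 75% with 39 and 70% with 35. The last two rest on assumed losses of about 11% and 20%. No actual shortfall is demonstrated, and with one or two losses it would be immaterial.

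The attendance defect is separate and needs no assumed loss rate, only the plain reading of section 2.1: a patient with complete first-phase data is removed from first-phase analyses for not attending later.

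The missing detectable difference and the use of beta where power must be meant are further faults in the same sentence of section 2.2. They are not what this point rests on.

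**What to change.** **Section 2.2.** Say that 44 is the number enrolled, and replace the claim of 80% for 44 with the power at the number of pairs expected to be analysable, using the centre's own attendance and HRV-rejection rates. For example, if 20% are expected to lack a valid rMSSD series at both evaluations: 44 enrolled, about 35 analysable pairs, about 70% power for the difference that 44 pairs would detect with 80%.

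**Section 2.1.** Apply the attendance rule by analysis. The first-phase correlation and ROC analyses use attendance in the first 24-session window only. The before-after change analysis keeps the rule over the whole protocol, including the 6-month second phase.

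**Cost.** A few sentences of wording, a less favourable stated power, and different Ns for the two analyses, each to be reported. No extra enrolment or procedures are needed.

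### The sample-size section gives beta as 80%, omits the rMSSD difference behind the 44, and did not size the study for its ROC and correlation aims

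*Protocol article*

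**What the plan says.** The protocol article's Sample size section bases the number on the rMSSD index "because it presents the highest sample number necessary for this study", and ranks it against two other variables, the 6-minute walking test and TNF-alpha. The inputs are then given in one sentence: "A standard deviation of 17 ms, alpha risk of 5%, and beta of 80% was considered for the calculus, which resulted in 44 subjects". The section names no difference to be detected, no test, no design (paired or two-group) and no sidedness.

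The Introduction sets three aims: how well risk stratification protocols predict signs and symptoms, how resting parameters correlate with them, and whether changes in those parameters influence them. Data analysis serves the first two with Pearson and intraclass correlations and ROC curves. It serves the third with repeated-measures ANOVA between moments, autonomic modulation included. For the ROC curves it says: "If the values of the area on the curve are ≥0.650, it will be considered significative". The same section fixes significance at 5% with 95% confidence intervals.

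**The concern.** There are two problems.

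1. The study's only sample-size justification contains a figure that is wrong as written. With the difference missing, nothing else in the section shows a reader which power was used.
2. The number comes from a difference in one parameter, whereas two of the three aims concern predicting, or being associated with, signs and symptoms. A reader who silently corrects beta to 20% will assume 80% power for those aims too.

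The article's Final considerations expect the results to guide which stratification protocol physical therapists use. If the study is too small for that question, a low or non-significant AUC could be read as showing that a protocol does not predict, when the data could not tell.

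**Working it through.** **Inputs from the article.** N = 44, SD = 17 ms, alpha = 5% and beta written as 80% (Sample size); observed-AUC cut-off 0.650 and 5% significance (Data analysis).

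**Assumptions.** Two-sided tests. The split of patients with and without signs or symptoms is not given; I take 22/22 as the most balanced case and go out to 9/35 and 35/9. The first figure of each split is the number with signs or symptoms.

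**1. The plan's own 44.** It cannot be reproduced forwards without a difference, so I solved for the difference that fits 44 (normal approximation).

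- Paired: (z_alpha + z_power) × 17 / √44
- Two groups of n: (z_alpha + z_power) × 17 × √(2/n)

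For 80% power the sum is 1.960 + 0.842 = 2.802; for 20% power it is 1.960 − 0.842 = 1.118.

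| Design | 80% power | 20% power (beta 80% taken literally) |
|---|---|---|
| 44 paired | 7.2 ms | 2.9 ms |
| 44 per group | 10.2 ms | 4.1 ms |
| 22 per group | 14.4 ms | 5.7 ms |

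All six are compatible with the stated inputs, so the text cannot show which was used.

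**2. Power at a true AUC of 0.65 against 0.50.** The null standard error is SE0 = √[(N+1)/(12·n1·n2)]. The standard error at AUC = A is Hanley–McNeil:

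SE1 = √{[A(1−A) + (n1−1)(Q1−A²) + (n2−1)(Q2−A²)]/(n1·n2)}, with Q1 = A/(2−A) and Q2 = 2A²/(1+A).

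At A = 0.65, Q1 = 0.4815, Q2 = 0.5121 and A² = 0.4225. At 22/22:

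- SE0 = √(45/5808) = 0.0880
- SE1 = √{[0.2275 + 21(0.0590) + 21(0.0896)]/484} = 0.0832
- Power using SE0 in the critical value: Φ[(0.15 − 1.96×0.0880)/0.0832] = 39%
- Power with a Wald test: Φ[0.15/0.0832 − 1.96] = 44%

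| Split | Null-SE power | Wald power | 95% CI half-width at 0.65 |
|---|---|---|---|
| 22/22 | 39% | 44% | 0.16 |
| 13/31 | 34% | 35% | 0.19 |
| 34/10 | 28% | 36% | 0.18 |
| 9/35 | 28% | 28% | 0.21 |
| 35/9 | 25% | 34% | 0.19 |

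A simulation of the rank test with normal scores gave 41% at 22/22. One-sided at 22/22, the formulas give 52-56%. For 80% two-sided power the total needed is 105-114 at an even split and 183 at 20:80.

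**3. The 0.650 cut-off against the stated 5%.** Using SE0, two-sided p < 0.05 needs an observed AUC above 0.5 + 1.96×0.0880 = 0.673 at 22/22. At 34/10, SE0 = √(45/4080) = 0.105 and the AUC must exceed 0.706. An observed 0.650 gives z = 0.15/0.0880 = 1.70, p about 0.09, at 22/22; and z = 0.15/0.105 = 1.43, p about 0.15, at 34/10. At every split in the table its 95% interval includes 0.50.

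**4. What 44 can detect with 80% power.** The true AUC runs from about 0.72 (22/22, Wald) to about 0.79 (9/35, null SE). For a correlation, tanh(2.80/√41) = 0.41.

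**The case against.** The defence makes several fair points.

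- **Nothing shows the study was planned at 20% power.** A reader might infer that from the beta figure, but mislabelling power as beta is the far likelier explanation. The 44 itself is not shown to be wrong; it can be neither confirmed nor refuted. The difference may stand in the full protocol, which an article condenses. That excuses the omission more than the wrong figure, which is printed.
- **Power is not simply below 40%.** That reading needs a two-sided test, an assumed split and the null-SE formula. The Wald formula gives 44% at 22/22, and one-sided variants exceed 50%. The range is what can be defended, and no variant comes near 80%.
- **The 0.650 value is a cut-off on the observed AUC,** not a planned true effect. Under that rule a predictor with a true AUC of 0.65 passes about 51% of the time, so the power figures are not the chance of meeting the plan's criterion. They are power at the plan's 5% level.
- **The claim of the highest number is qualified.** The text limits the comparison to the walking test and TNF-alpha. A reader might take it to cover the ROC analysis; the sentence makes no such comparison.
- **An rMSSD difference is relevant to the study.** It serves the ANOVA between moments under the third aim. It would be wrong to say the number matches no planned analysis.
- **Loss of usable patients is not quantified.** The attendance exclusion, and the rule that "only series with more than 95% of heart sinus beat are going to be included in the study", could reduce the 44, but the article gives no rate, and 44 may already mean evaluable patients. I put no figure on it.

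What remains is the wrong beta, an unreproducible number, and a sample not derived for the ROC and correlation aims.

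**Conclusion.** The point holds in this limited form. The beta figure is wrong as printed, and without the rMSSD difference the 44 cannot be checked. The number was derived for an rMSSD difference and ranked against two other parameters only. For the ROC aim it gives roughly 25-45% two-sided power at a true AUC of 0.65, and an observed AUC at the plan's own cut-off does not reach the plan's own 5% level. The power range rests on the assumed splits, on two-sided testing and on the choice of standard error; the shortfall from 80% does not depend on those choices. The documents do not support the stronger conclusions that the study was designed at 20% power or that the 44 is an arithmetic error.

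**What to change.** 1. In Sample size, replace the beta figure with power 80% (beta 20%), if that is what was used, and state the rMSSD difference, whether 17 ms is the SD of a change or between patients, the test and its sidedness.
2. Limit the wording about the highest number needed to the three parameters actually compared.
3. Add what 44 delivers for the other aims, with the split labelled as an assumption (22/22 out to 9/35 or 35/9): 80% two-sided power only for a true AUC of about 0.72-0.79 or an absolute correlation of about 0.41, and a 95% CI half-width of about 0.16-0.21 at an AUC of 0.65.
4. In Data analysis, report each AUC with its 95% interval, and describe one whose interval includes 0.5 as inconclusive, whether or not the estimate passes 0.650.

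The cost is a text correction. No extra patients and no change of design are needed. The downside is that the study's stated capability becomes less favourable.

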### Ethical aspects

2.3

The volunteers are going to be previously informed about the objectives and procedures of the study and, after agreeing to participate, they will sign a consent form. All the procedures that are going to be used in the study were approved by the Committee for Ethics and Research of the São Paulo State University (UNESP), School of Technology and Sciences, Presidente Prudente (CAAE: 79213417.0.0000.5402).

### Study design

2.4

This study is going to be divided in 3 phases. Initially, all the volunteers are going to have their medical records analyzed, and information about the sample characterization and medical examinations are going to be extracted. Two independent blinded and trained measurers are going to realize the risk stratification of the volunteers, using the protocols described into the literature review of Silva et al.^[39]^ Following this, clinical (cardiorespiratory parameters and autonomic modulation), physical [maximum isometric resistance (MIR), maximum isometric voluntary contraction (MIVC), cardiorespiratory fitness, and physical activity level], and biochemical [interleukin (IL)-6, TNF-alpha, and IL-10] parameters are going to be evaluated by a blinded and trained measurer and the subjects are going to be accompanied during 24 sessions of their CRP routines, to register the appearance of their signals and symptoms.

In the second phase, the volunteers are going to realize their normal CRP routines for 6 months. In the third phase, the clinical, physical, and biochemical parameters, described above, are going to be evaluated by a blinded and trained measurer and the volunteers are going to be accompanied for more 24 sessions of their CRP routines, to register the appearance of their signals and symptoms as well.

The description of the phases and the volunteers that will be included in each one of them are reported at Fig. 1.

